#### Depression in patients with advanced cancer and the role of inflammation

Depression disorder contribute to reduced quality of life in patients with advanced cancer [41]. Depression disorder is common among cancer patients with a prevalence that varies from 5 to 30% between studies [42]. A particular challenge for assessment of depression in patients with advanced cancer is the somatic depression symptoms (fatigue, psychomotor retardation, appetite disturbance and sleep disturbance) which constitute 4 out of 9 diagnostic criteria for depression disorder. In patients with advanced cancer the somatic depression symptoms can result from depression, the cancer, treatment effects, or a combination of these factors [43].

In a cross-sectional study that also controlled for disease load, we demonstrated that by only using the 5 psychological depression symptoms for defining depression disorder, we could circumvent the challenge of the overlap between the somatic depression symptoms and symptoms of the cancer [44] [45]. However, our study was cross-sectional thus limiting the possibility to assess causality [44]. Studying the development of depression disorder and each of the depression symptoms over time with control for disease and treatment(s) can provide evidence-based guidance on how to best assess depression in patients with advanced cancer.

Patients with advanced cancer and depression disorder have more somatic symptoms including pain compared to non-depressed patients, but no appropriately designed studies to examine a possible causal relationship have to our knowledge been published. Clinically, a common observation is that long-lasting pain is associated with increased levels of depression symptoms. Still the direction of causality is not established and might be bidirectional. The relation between pain and depression has to be studied in a longitudinal design in order to better understand how they are related.

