*Outcome*: Cachexia is defined as a) weight loss > 5% over past 6 months (in absence of simple starvation); or b) body mass index (BMI) < 20 and any degree of weight loss > 2%; or c) appendicular skeletal muscle index consistent with sarcopenia (males < 7・26 kg/m2; females < 5・45 kg/m2) and any degree of weight loss > 2% [38]. Cachexia severity is assessed as degree of weight loss and EORTC QLQ C15 PAL physical function and appetite loss.

*Statistical method*: Fist, we will perform a cross-sectional analysis in the baseline parameters using a logistic regression with cachexia as outcome, and the various inflammatory markers as explanatory variables. Second, we will investigate the association between changes in inflammatory markers over time and cachexia severity using mixed linear modelling.

**Research question 4:** Which inflammatory substances are associated with depression in cancer patients?

*Objective*: To explore the associations between serum concentrations of inflammatory substances and depression.

*Outcome*: Depression is measured by the PHQ-9 questionnaire [57]. The PHQ-9 includes 9 items identical to the diagnostic criteria (i.e. the depression symptoms) for depression disorder. For the purpose of these analyses we will use depressive disorder as defined by the PHQ-9 recommended sum score calculation, and symptom by symptom in the PHQ-9 score in associations of serum concentrations of inflammatory biomarkers during a period of 1 year form inclusion.

*Statistical method*: We will use repeated measurements and a linear mixed effect model to perform the analyses.

**Research question 5:** Which are the clinical predictors and biomarker predictors of development of cachexia in patients with metastatic cancer disease?

*Objective*: To obtain demographic and clinical data and biomarkers in a homogenous population of patients with metastatic cancer, and within a prospective, longitudinal follow-up study observe which factors predicting the development of severe cachexia during one-year follow-up.

*Outcome*: Cachexia is defined as for research question 3.

*Statistical method*: As the purpose is to evaluate development of cachexia, only patients without cachexia at baseline will be included in this analysis. A Cox regression will be used to evaluate baseline predictors of cachexia development.

**Research question 6**: What is the relationship between pain reduction and depression in patients receiving RT for CIBP?

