*Objective*: RT is expected to reduce pain in a substantial number of patients. This creates a possibility to study the relationship between depression and pain longitudinally in an experimental-like design in which one variable (pain) is manipulated and the effect on another related variable (depression) is studied.

*Outcome*: Depression is measured as for Research question 4.

*Statistical method*: Longitudinal analyses with repeated measurements analyzed with a linear mixed effect model.

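### Research questions 4 and 6 name only a linear mixed model for a categorical depression outcome and single PHQ-9 symptoms, and the disorder definition keeps the somatic items that the background warns about

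*Protocol article*

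**What the plan says.** Under research question 4 in Outcome and statistical analyses, the PHQ-9 is described as follows: "The PHQ-9 includes 9 items identical to the diagnostic criteria (i.e. the depression symptoms) for depression disorder". The outcomes are then fixed: "we will use depressive disorder as defined by the PHQ-9 recommended sum score calculation, and symptom by symptom in the PHQ-9 score", each related to serum inflammatory markers over one year. The method is one sentence: "We will use repeated measurements and a linear mixed effect model to perform the analyses". Research question 6 measures depression in the same way and gives the method as: "Longitudinal analyses with repeated measurements analyzed with a linear mixed effect model".

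The background section on depression in advanced cancer reports: "Depression disorder is common among cancer patients with a prevalence that varies from 5 to 30% between studies". It names fatigue, psychomotor retardation, appetite disturbance and sleep disturbance as the somatic symptoms, "which constitute 4 out of 9 diagnostic criteria for depression disorder", and says of advanced cancer that "the somatic depression symptoms can result from depression, the cancer, treatment effects, or a combination of these factors". On the group's own previous cross-sectional study it says that "by only using the 5 psychological depression symptoms for defining depression disorder, we could circumvent the challenge of the overlap".

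**The concern.** There are two separate difficulties.

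**Model and outcome.** A disorder is present or absent, and a linear mixed model assumes a continuous outcome with normal residuals of constant variance. For a yes/no outcome the variance is p(1−p). It therefore moves with any marker that is associated with the outcome, and a straight line can leave the 0 to 1 range. Single questionnaire items raise a similar doubt if they have only a few ordered levels.

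**Definition of the disorder.** The explanatory variables are inflammatory markers. The background links fatigue, sleep and appetite changes to cytokine activation (sickness behaviour). It also warns that inflammation may simply accompany more severe cancer. If the disorder is built from a sum that includes those symptoms, a marker may be associated with it through the somatic items alone. The result would then be reported as a link with depression. In research question 6, where depression is related to pain reduction, the outcome has the same composition.

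**Working it through.** The protocol gives no sample size, power or significance level for research questions 4 or 6, so there is no planned figure to reproduce. The check is mainly a comparison of sections.

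**1. Is the disorder a category?** The background gives it a prevalence (5 to 30%) and contrasts patients who have it with patients who are not depressed. Research question 4 uses the same term for its outcome. The plain reading is yes/no, although no cut-off is printed.

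**2. How does the protocol treat comparable outcomes?**

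| Research question | Outcome | Model named |
|---|---|---|
| 2 | Pain intensity, numeric scale | Linear mixed model or GEE |
| 3, first part | Cachexia, yes/no | Logistic regression |
| 3, second part | Cachexia severity over time | Mixed linear model |
| 4 | Depressive disorder; single PHQ-9 symptoms | Linear mixed model only |
| 6 | As for 4 | Linear mixed model only |

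Research question 3 separates the yes/no outcome from the graded one. Research questions 4 and 6 do not.

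**3. Both readings of the disorder outcome.**
- If it is yes/no, the named model does not match it.
- If the continuous sum was meant, the linear mixed model is suitable for that outcome, but the label is wrong. The question about single symptoms remains.

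The text needs correcting either way.

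**4. How much could a straight line mislead?** This is an illustration, not a finding about this cohort. Assume one standardised, normally distributed marker x, a true logistic relation with an odds ratio (OR) of 1.5, 2 or 3 per standard deviation, and a prevalence p in this cohort at either end of the quoted range. It is cross-sectional, with no random effects. The best straight line is p + s·x, with slope s found numerically. It is negative where x < −p/s, so the share of patients with a negative fitted probability is Φ(−p/s).

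| p | OR per SD | s | p/s | Share below zero |
|---|---|---|---|---|
| 0.05 | 1.5 | 0.0191 | 2.62 | under 0.5% |
| 0.05 | 2 | 0.0321 | 1.56 | about 6% |
| 0.05 | 3 | 0.0486 | 1.03 | about 15% |
| 0.30 | 1.5 | 0.0823 | 3.65 | under 0.1% |
| 0.30 | 2 | 0.1329 | 2.26 | about 1% |
| 0.30 | 3 | 0.1890 | 1.59 | about 6% |

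The misfit is negligible for weak associations and noticeable for a rare disorder with a strong one.

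**5. Somatic share.** 4/9 = 44% of the criteria. This is also the share of the maximum sum if all items carry equal weight, which is an assumption.

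**6. Is the overlap dealt with elsewhere?** In part. The symptom-by-symptom analysis shows somatic and psychological items separately. It does not alter the disorder outcome, which still includes all nine.

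**The case against.** The best defence has four parts.

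- **The yes/no reading is an interpretation.** No cut-off is printed, and the wording about a sum score could mean the continuous sum, for which the named model is suitable. The item response scale is not printed either. This stands as a limit on certainty. It does not remove the point, because the text calls the outcome a disorder.
- **This is a condensed article.** Cut-offs and model details may be in the full protocol or analysis plan. That is fair, and the missing cut-off is not held against it. The point rests on what is printed: a named outcome and a named model that do not fit together.
- **The aim is to explore associations, not to predict individual risk.** Fitted values outside the range then matter little. This largely stands for weak associations, as the table shows.
- **The overlap is not ignored.** The background proposes following the disorder and each symptom over time, and research question 4 does both. An association carried only by fatigue, sleep or appetite should show in the item results. A reader might infer that the study overlooks the problem, or that the 5-symptom definition must be the main outcome. The documents support neither. The earlier study was cross-sectional, and the background treats the best way of assessing depression as still open.

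Two further inferences are also unsupported. The 5 to 30% prevalence range is a spread between studies, so it does not show unequal variance within this cohort. Multiplying the listed markers by the disorder and nine symptoms to count expected false positives needs a significance level, one test per pair and all null hypotheses true. None of these is stated for an analysis described as exploratory.

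**Conclusion.** The point holds in a limited form. On the plain reading, research questions 4 and 6 give a categorical outcome a model meant for a continuous one, although research question 3 makes the distinction correctly. The disorder outcome also keeps all nine criteria, 44% of them somatic, without the 5-symptom definition that the background credits with avoiding the overlap. The item analysis mitigates this but does not remove it.

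The conclusion rests on two assumptions: that the disorder is meant as yes/no, and, for single symptoms, that items are scored in a few ordered levels. The effect on results cannot be sized from the document. In the illustration, negative fitted probabilities range from practically none to about 15% of patients, depending on assumed prevalence and odds ratio. Both questions are secondary and exploratory, so the primary endpoint, its logistic model and the sample size are untouched.

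**What to change.** In research questions 4 and 6, name each depression outcome and its model:

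- **Continuous PHQ-9 sum score:** linear mixed model, as now.
- **Depressive disorder, yes/no at a stated cut-off:** mixed-effects logistic model or logistic GEE.
- **Single PHQ-9 symptoms:** ordinal mixed model, if the items are scored in a few ordered levels.
- **Sensitivity outcome, prespecified for both questions:** depression defined on the 5 psychological symptoms, with a logistic model if it is used as yes/no and a linear mixed model if it is used as a continuous score.

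The PHQ-9 is scheduled at every visit (Table 1), so no new data are needed. The cost is revised wording and a little more analysis work. Settling this before the analysis also prevents a choice between sum, disorder and items after the results are seen.

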### Ethics

A signed consent will be obtained from all participants by an investigator at each site. The study will be carried out in accordance with ICH GCP and the World Medical Association Declaration of Helsinki (1964) and its’ revisions (Tokyo 1978, Venice 1983, Hong Kong 1989, South Africa 1996 and Edinburgh 2000). The study is approved by The Regional Committee for Medical and Health Research Ethics, REC Central Norway, and by the regulatory authorities at each trial site. If modifications to the protocol, amendments will be applied for to the regional ethics committee and after approval distributed to all local study investigators.

RT is indicated and will be given regardless of whether the patients choose to participate in the study or not. Thus, study participation means that patients consent to report symptoms and have their blood drawn. The volumes of blood samples are limited (less than 50 ml) and give no extra risk for anemia. Thus, the study includes no interventions that increase the risk for the patients. Data are handled anonymously. The database used for analyses only identify each patient by a study number. The linkage between study number and patient identity is in a document and / or memory stick stored in a safe at each study center.

### Organizational issues

A Trial Steering Group will oversee the running of the trial. Members of the trial steering group include the chief principal Investigator, the principal Investigators of each centre, the Clinical Trial coordinator, and the trial statistician. After completion of the inclusions the Trial Steering Group will consists of the chief principal investigator, the principal investigators at all sites including 100 patients or more, and the trial statistician.

The coordinating centre will administer the study. This includes development and administration of Case report forms (CRFs), monitoring of data quality and preparation of the final study report. (CRFs) will be supplied by the coordinating centre. Specific queries about data will be addressed to the clinical trial coordinator at each study centre.

The results will be published in peer-reviewed journals. Authorship is based upon the Vancouver rules. All manuscript will be prepared by the researchers. The trial steering group will make decision related to use of data for publication. The principal investigator has access to all data. Access to researchers will be decided based upon the actual need for access relevant for analyses. Access to anonymously participant-level data set will be supplied depending on the journal policies.

## Discussion

Clinical trials in cancer are mostly carried out to evaluate and compare different treatment strategies, medications and interventions. Whiles the effect of RT to treat CIBP is well documented, there is limited information about which characteristics that differs among responders versus non-responders. To achieve reliable predictors for treatment response, studies with large patient materials that obtain follow-up visits are needed. In this study, detailed clinical information, inflammatory and bone biomarkers will be collected before RT. These are all data and analyses that could be included in routine clinical practice to better select patients likely to have RT response. This can reduce the administration of non-efficacious RT. Patients will benefit from not spending time on futile treatment and not risking adverse effects related to RT as well as not delaying alternative pain treatments.

Our research group has in the last decade published several papers on cancer pain and the relationship between pain and other cancer symptoms to improve cancer pain classification [59–61]. International collaboration have also developed the Edmonton classification for cancer pain [56, 62]. The PRAIS study will include a large cancer patient population with advanced, but not terminal, cancer disease that will be used to investigate which clinical characteristics and biomarkers are associated with other cancer related symptoms. We will explore the longitudinal associations for pain, depression and cachexia with clinical characteristics, and biomarkers.

The investigation of the role of inflammation in respect to RT response for patients with CIBP and other cancer related symptoms like pain intensity, depression and cachexia is of a more explorative character. Current literature is mostly based on pre-clinical studies that needs to be investigated further in human studies. This study will include patients who all have on-going CIBP, which is a more homogenous population than usually seen in cancer pain studies. The patients will receive a standardized intervention expected to give pain relief in about 60% of the patients, and the study is therefore a unique possibility to identify which inflammatory substances that are associated with changes in cancer pain intensity. Improved knowledge about the pathophysiology of bone cancer pain and the role of inflammation can identify potential targets for therapy. The longitudinal design of the study also makes it possible to study the relationship between inflammation and symptoms of depression and development of cachexia. If biological factors are detected they could be used to identify which patients who could benefit from therapy directed towards hindering or delaying the development of severe cachexia or treatment of depression in cancer patients.

### Expected limitations

As for all studies on palliative cancer patients we expect the number of drop-outs and missing data to be relatively high. A reason for drop-out before evaluation of treatment response may be that the patients are too sick or because of high symptom burden. These patients cannot be included in the predictive analyses as they are not missing at random and may bias the results. The patient inclusion is also for practical reasons not consecutive and the sample size of 600 do not allow for a validation sample analyses. Also, in order to assess the adverse effects from RT, a day-to-day evaluation of symptoms after RT would have given important information but were not performed in order to simplify data collection for the patient population.

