### Power consideration

The sample size is based upon the primary outcome; response to RT for pain [18]. The analyses plan includes up to 29 independent clinical variables (see previous sections for variables marked with an asterisk.) A full statistical estimate of sample size requires knowledge of the variance-covariance matrix, which was not available at the planning stage of this study. Therefore, the widely-used rule of thumb of 10 x number of variables was adopted. This reasoning resulted in a sample size of 290. Based upon experience, interactions will arise which increases the needed number of patients, and up to 20% of patients were expected to be lost to follow-up. To account for this, the number of needed patients was set to 600. The original protocol plan was to include a validation sample of 1/3 of patients resulting in a total number of 1000 included patients. But because of slow recruitment, we had to close the study after 600 recruited patients, and the analyses will therefore be performed without the planned validation sample.

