### Outcome and statistical analyses

For all planned analyses baseline data will be presented with descriptive statistics; continuous variables as mean with standard deviation and categorical variables as frequency with percentages. A detailed overview of research questions and statistical analyses are described in the following section. All analyses will be performed using SPSS v 23 (IBM Corp. Armonk, NY) and STATA v 16 (Stata Corporation LP; College Station, TX, USA).

**Research question 1:** Which are the clinical predictors and biomarkers predictors of pain response to palliative RT for CIBP?

*Objective*: To obtain demographic, clinical data and biomarkers before start of RT and compare with RT response for pain in order to develop a classification system relevant for predicting RT response.

*Outcome*: Primary endpoint is response to RT defined as at pain reduction of worst pain score of two or more at the treated site on the 11-point NRS together with no increase in analgesic intake, or a reduction in opioid intake of at least 25% from baseline without an increase in worst pain score at the treated site [18]. Patients with two or more radiation locations are defined as responders if they respond in one of the included sites. Patients who die before the first assessment (3 weeks after RT), will be defined as non-responders because these patients have not benefited from RT. Patients with missing data on outcome measurements including pain intensity at the treated site or the use of analgesic medications will not be included in the analyses.

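### Non-random drop-out is given as the reason to exclude patients too ill to be evaluated, but in that situation exclusion does not remove bias and can overstate predicted response

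*Protocol article*

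**What the plan says.** Under Expected limitations the article states that "we expect the number of drop-outs and missing data to be relatively high". It then offers an explanation: "A reason for drop-out before evaluation of treatment response may be that the patients are too sick or because of high symptom burden". The consequence drawn is: "These patients cannot be included in the predictive analyses as they are not missing at random and may bias the results".

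The operative rule is in Outcome and statistical analyses, research question 1: "Patients with missing data on outcome measurements including pain intensity at the treated site or the use of analgesic medications will not be included". The same paragraph treats early death differently: "Patients who die before the first assessment (3 weeks after RT), will be defined as non-responders because these patients have not benefited from RT".

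Power consideration gives the only figure for loss: "up to 20% of patients were expected to be lost to follow-up". The analysis is a logistic regression whose significant variables become a response score. Karnofsky status and CRP are among the candidate predictors.

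**The concern.** A complete-case logistic model is protected when the chance of a missing outcome depends only on covariates in the model. It is not protected when that chance also depends on the outcome. The article asserts non-random missingness, which is the unprotected case, and uses it as the reason to exclude.

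The product at stake is the response score, which is meant to spare patients futile RT. The Background reports better response with higher performance status, and links raised CRP to more advanced disease. Patients lost through illness are therefore plausibly concentrated among the frail, for whom the score matters most. If the non-responders among them are lost more often than the responders, the score will be too optimistic for that group.

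There is also an inconsistency of principle. A patient who dies before week 3 counts as a non-responder because RT brought no benefit, while a patient who is alive but too ill to report at week 3 is left out. Similar deterioration is handled in opposite ways.

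**Working it through.** **Inputs.** From the article: N = 600; up to 20% lost to follow-up (Power consideration); pain relief in about 60% (research question 2 and Discussion). The article gives no figure for patients without an evaluable primary outcome, so there is no plan figure to reproduce. The missing share and the response rate among the missing are assumptions throughout.

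**1. Response rate.** With missing share *d*, complete-case rate 0.60 and response *q* among the missing, the all-patient rate is (1 − *d*) × 0.60 + *d* × *q*. At *d* = 0.20, 120 of 600 are missing and 288 of 480 observed patients respond.

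- *q* = 0.20: 0.80 × 0.60 + 0.20 × 0.20 = 0.52
- *q* = 0: 0.80 × 0.60 = 0.48
- *q* = 1: 0.48 + 0.20 = 0.68

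The bounds are 54% to 64% at *d* = 0.10 and 42% to 72% at *d* = 0.30. In the other direction, if the true rate is 60% and 20% are missing, the complete-case rate is (0.60 − 0.20*q*)/0.80, which is 65%, 70% or 75% for *q* = 0.40, 0.20 or 0.

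**2. One binary predictor (all inputs assumed).** Let 30% have low performance status, with true response 45% (low) and 66% (high). Missingness for non-responders/responders is 45%/15% (low) and 20%/8% (high).

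- True OR, high v low: (0.66/0.34)/(0.45/0.55) = 2.37
- Complete-case OR: [0.66 × 0.92/(0.34 × 0.80)]/[0.45 × 0.85/(0.55 × 0.55)] = 1.77
- The distortion factor is (0.92/0.80)/(0.85/0.55) = 0.744. If the two ratios were equal, the OR would stay at 2.37.
- Observed fraction: 0.70 × (0.6072 + 0.2720) + 0.30 × (0.3825 + 0.3025) = 0.821
- Complete-case response: (0.70 × 0.6072 + 0.30 × 0.3825)/0.821 = 65.8%, against a true 0.70 × 0.66 + 0.30 × 0.45 = 59.7%
- Predicted response at low status: 0.3825/0.685 = 56%, against a true 45%

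**3. Dependence on the mechanism.** This is a simulation of 1,000,000 records with one standardised frailty predictor (log-odds slope −0.5, OR about 0.61), true response 60% and 20% missing outcomes. Brackets give the missingness log-odds coefficients for frailty, non-response and their interaction.

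| Drop-out depends on | Complete-case rate | OR, all → complete cases | Predicted response at +1 SD frailty, all → complete cases |
|---|---|---|---|
| Frailty only (1, 0, 0) | 62% | 0.61 → 0.61 | 0.48 → 0.48 |
| Non-response only (0, 1.5, 0) | 67% | 0.61 → 0.61 | 0.48 → 0.56 |
| Both, additive (1, 1.5, 0) | 68% | 0.61 → 0.74 | 0.48 → 0.60 |
| Both, interaction (0.3, 0.5, 1.0) | 66% | 0.61 → 0.79 | 0.48 → 0.59 |
| Both, interaction (1, 1.5, 0.5) | 69% | 0.60 → 0.83 | 0.48 → 0.64 |

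Coding every missing outcome as non-response is not neutral either. Across these scenarios it gives rates of 50% to 55% against a true 60%, and ORs of 0.48 to 0.65 against about 0.61.

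**The case against.** The strongest defence is that the sentence stands under a limitations heading and may have been meant to say that losing these patients could bias the results. That reading is possible. As worded, though, the threat of bias is the reason for leaving them out, and the rule under research question 1 carries the exclusion out.

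A second defence is that the planned model already includes Karnofsky status, worst pain, depression, nausea, opioid dose and CRP. If drop-out depended only on such covariates, the complete-case model would be sound, as the first row of the table shows. This stands, but it is a missing-at-random argument, and the article asserts the opposite.

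Third, the 20% is general loss to follow-up in a 52-week study, not missing primary outcome, and deaths before week 3 are retained. The direction is also not documented: the Background notes that one of two papers associated high baseline pain and morphine use with response. Both points stand. They are why the figures are illustrations and why the bounds run in both directions.

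Four stronger readings are tempting but not supported:

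- *The two rules contradict each other.* They cover separate groups, and death is a known event while a missing questionnaire leaves response unknown. The inconsistency is one of principle.
- *The odds ratios are biased.* This depends on the mechanism; in two of the five scenarios they are not.
- *Patients who die after week 3 disappear from the analysis.* That would follow only if response were judged later than week 3. The article names no visit for the endpoint, and a patient assessed at week 3 has data.
- *Missing predictor values will also empty the data set.* The article states no rule for missing predictors, and this may be left to an analysis plan.

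**Conclusion.** The concern holds in conditional form. Non-random missingness cannot justify the exclusion, because it is the condition under which complete-case analysis loses its protection. If non-responders are more often missing, the response rate is overstated; if this also holds among patients with the same covariates, so are the predicted probabilities. Odds ratios for frailty-related predictors can be distorted as well when drop-out depends jointly on frailty and non-response. If drop-out depends only on modelled covariates, the model is unbiased, although the crude rate may still shift.

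On size: an apparent 60% could be 52% with 20% missing and 20% response among them, and anything from 48% to 68% without an assumption about the missing. Where non-response drives drop-out, simulated predicted response for a frail patient rises from about 0.48 to between 0.56 and 0.64. These sizes rest on the assumed missing share and mechanism; the article fixes neither. The matter should be settled before the primary analysis, because it determines what the response score can claim.

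**What to change.** 1. Reword the sentence under Expected limitations so that it says leaving these patients out may bias the results.
2. Name the assessment visit for the primary endpoint, and apply the rule that death is non-response up to that visit.
3. Include all patients who received RT by multiple imputation, using the baseline predictors, with later-visit pain, medication and survival as auxiliaries. Without informative auxiliaries, imputing the outcome largely reproduces the complete-case fit, and later pain scores may be absent in the sickest patients.
4. Because standard imputation assumes missing at random, it does not by itself answer the stated problem. Pre-specify delta-adjusted imputation over a stated range, and an analysis that codes documented inability to report through illness as non-response. Present the latter as a bound, not a correction.
5. Keep the complete-case analysis as a comparison, and report excluded patients by reason with their baseline characteristics.

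Recruitment is closed, so the cost is wording and some programming, with no change to recruitment or sample size. The downside is reliance on imputation assumptions, which the analyses in step 4 put to the test.
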